**Total volume of blood draws**

A total of 372 mL of blood including discard will be collected from each participant over the course of the study. This amount of blood does not exceed the amount of blood taken by the American Red Cross or a single donation of 450 ml or one pint over any given 8-week period. A healthy person can safely donate this amount of blood every 8 weeks. All the tests performed in this protocol are summarized in the following table:

**Schema of Blood Collection/Analysis**

|  | **Visit 1**  **(T0)** | **Visit 2**  **(T1)** | | | | | | **Visit 3**  **Inpatient (T2)** | | | | | | | | | | | | | **Visit 4**  **(T3)** |
| --- | --- | --- | --- | --- | --- | --- | --- | --- | --- | --- | --- | --- | --- | --- | --- | --- | --- | --- | --- | --- | --- |
|  | Outpatient | Outpatient | | | | | | Day 1 | | | | | | | Day 2 | | | | | | Out |
| **Type of Visit** | Screening | Base | 0 | 2 | 4 | 6 | 8 | Base |  | 1 | 2 | 4 | 8 | 12 | 24 | 0 | 2 | 4 | 6 | 8 | 2 weeks |
| Blood tests1 | **X** |  |  |  |  |  |  |  |  |  |  |  |  | **X** |  |  |  |  |  | **X** |
| Lipid Tolerance Test2 |  | **X** |  | **X** | **X** | **X** | **X** |  |  |  |  |  |  | **X** |  | **X** | **X** | **X** | **X** |  |
| G6PD activity3 | **X** |  |  |  |  |  |  |  |  |  |  |  |  |  |  |  |  |  |  |  |
| UA + Hypoxanthine4 |  |  |  |  |  |  |  | **X** | **X** | **X** | **X** | **X** | **X** | **X** |  |  |  |  |  | **X** |
| PAXgene (RNA)5 |  |  |  |  |  |  |  | **X** |  |  |  |  | **X** | **X** |  |  |  |  |  | **X** |
| DNA Extraction6 |  | **X** |  |  |  |  |  | **X** |  |  |  |  |  |  |  |  |  |  |  |  |
| Inflammatory markers7 |  | **X** |  | **X** | **X** | **X** | **X** | **X** | **X** | **X** | **X** | **X** | **X** | **X** |  | **X** | **X** | **X** | **X** | **X** |
| Antioxidant markers8 |  |  |  |  |  |  |  | **X** | **X** | **X** | **X** | **X** | **X** | **X** |  |  |  |  |  | **X** |
| Ox damage markers9 |  |  |  |  |  |  |  | **X** | **X** | **X** | **X** | **X** | **X** | **X** |  |  |  |  |  | **X** |
| Blood volume draw | 26.5 ml | 45 ml | | | | | | 256.5 ml | | | | | | | | | | | | | 49 ml |

**1.** Complete CBC with differential count, Glucose, BUN, Creatinine, UA, LDK, CPK, Electrolytes (NA+, K+, CL-; CA++, MG+), AST, ALT, ALP, Albumin, Globulins, Bilirubin (total and direct), Haptoglobin, LDL-HDL and total cholesterol, Triglycerides, and CRP.

**2.** Measures obtained at each point: IL-6, IL-6sr, TNF-α, TNF-r1, TNF-r2, sgp 130, and hsCRP +Tryglycerides+1 mL of serum for banking purposes.

**3.** G6PD activity, once in the study.

**4.** UA+Hypoxanthine..

**5.** PAXgene, 5 mL per point. Total volume for 4 points 20 mL.

**6.** DNA extraction, once in the study: Total volume 5 mL.

**7.** Measures obtained at each point: IL-1ra, IL-6, IL-6r, IL-18, IL-1β, TNF-α, TNF-r1, TNF-r2, sgp130 and hsCRP + 1ml of serum for storage.

**8.** Measures obtained at each point: Vitamin C, Carotenoids and Selenium + 1ml of serum for storage.

**9.** Measures obtained at each point: F2-Isoprostane + oxidized/reduced glutathione ratio + 1ml of serum for storage.

Schema of Urine Collection/Analysis

|  | **Visit 1**  **(T0)** | **Visit 2**  **(T1)** | | | | | | **Visit 3**  **Inpatient (T2)** | | | | | | | | | | | | | **Visit 4**  **(T3)** |
| --- | --- | --- | --- | --- | --- | --- | --- | --- | --- | --- | --- | --- | --- | --- | --- | --- | --- | --- | --- | --- | --- |
|  | Outpatient | Outpatient | | | | | | Day 1 | | | | | | | Day 2 | | | | | | Out |
| **Type of Visit** | Screening | Base | 0 | 2 | 4 | 6 | 8 | Base |  | 1 | 2 | 4 | 8 | 12 | 24 | 0 | 2 | 4 | 6 | 8 | 2 wks |
| Urine Analysis1 | **X** |  |  |  |  |  |  |  |  |  |  |  |  |  |  |  |  |  |  | **X** |
| Urine Toxicology2 | **X** |  |  |  |  |  |  |  |  |  |  |  |  |  |  |  |  |  |  |  |
| Urine Pregnancy3 | **X** | **X** |  |  |  |  |  | **X** |  |  |  |  |  |  |  |  |  |  |  | **X** |
| Urine Sp. Gravity4 | **X** |  |  |  |  |  |  | **X** | **X** | **X** | **X** | **X** | **X** | **X** |  |  |  |  | **X** |  |
| Urine pH5 | **X** |  |  |  |  |  |  | **X** | **X** | **X** | **X** | **X** | **X** | **X** |  |  |  |  | **X** |  |
| Urinary UA6 |  |  |  |  |  |  |  | **X** | **X** | | | | | **X** |  |  |  |  |  | **X** |

**1.** Complete urine analysis and sediment on morning spot urine.

**2.** General toxicology, including alcohol

**3.** Rapid pregnancy test

**4 and 5**. Specific gravity and pH can me measured in the clinic, recovering most of the urine used for the measure.

**6.** The only note here is for the 12 hours urine collection. The participant is asked to urinate before the administration of the study drug. All urines are collected. Last urination at 12 hours from the beginning of the infusion.

**6. RISKS/DISCOMFORTS**

Risk associated with the administration of UA solution: UA is a physiological constituent of cells and blood in humans. Based on published studies, I.V. administration of UA 1,000 mg and 500 mg in 250 ml of 0.1% lithium carbonate/ 4% dextrose solution over a 60 minute period was not associated with any adverse event, change in blood pH, clinical, hemodynamic and biochemical parameters. In a total of 44 persons, the administration of UA 500 mg was associated with an average increase of circulating levels between 3 and 4 mg/dL which creates a transitory increase of the UA concentration. The transitory increase of the UA concentration did not cause any risk, while it was associated with increased plasma antioxidant activity, reduced oxidative stress marker and better endothelial function. There is a very low risk that UA may precipitate in renal tubules and cause kidney damage. This risk is minimized by administering a dose of UA that should not increase the UA concentration above the solubility threshold, checking the urine specific gravity is below 1015 before the administration, ensuring abundant intake of water, inducing a mild urine alkalinitation (by administering orally sodium bicarbonate) and monitoring the urine pH and specific gravity.

Risk associated with the administration of Rasburicase: Potential side effects are listed in the table below. These side effects have been observed in 703 patients affected from leukemia, lymphoma, and solid tumor malignancies who are receiving anti-cancer therapy. The most severe side effects of Rasburicase administration are hypersensitivity reactions including anaphylaxis (<1%), and methemoglobinemia (<1%).

| **Serious Adverse Reaction** | Percentage (%) of Subjects (total n=703) |
| --- | --- |
| Allergic reactions including anaphylaxis | <1 |
| Rash | <1 |
| Hemolysis | <1 |
| Methemoglobinemia | <1 |
| Fever | 5 |
| Neutropenia with fever | 4 |
| Respiratory distress | 3 |
| Sepsis | 3 |
| Neutropenia | 2 |
| Mucositis | 2 |
| **Adverse Reaction** | Percentage (%) of Subjects (total n=436) |
| Vomiting | 50 |
| Fever | 46 |
| Nausea | 27 |
| Headache | 26 |
| Diarrhea | 20 |
| Mucositis | 15 |
| Rash | 13 |

Note: an antibody response to a single dose of rasburicase (immunogenicity) has also been observed. To the date of this protocol, the immunogenicity issue is not applicable to our study since the drug is not approved for the treatment of adults.

The risk of blood drawing: There is a slight risk of pain, bruising around the site where blood is drawn and rarely bleeding or infection. To minimize this risk, the routine blood–drawing protocol will be followed and pressure will be applied to the site. Some people experience feelings of lightheadedness or dizziness after having blood drawn. To reduce the risk of falling, we will monitor the subject closely and ask about these symptoms before we allow them to stand. The samples collected will be used to monitor the subject’s medical condition and for research purposes.

Risk of Basal Metabolic Rate: A little discomfort may be due to mask. However, this discomfort is only momentary, lasting only few minutes.

Risk of Oral Lipid Tolerance Test: Rarely eating a fatty meal may lead to a temporary sense of abdominal fullness and discomfort, nausea, vomiting, or diarrhea.

Risk of resting EKG: There may be slight skin irritation from the electrodes. There are no other risks associated with this test.

Risks of MRI, Functional MRI, and MRS. The effects of magnetic fields in an MR scanner have been extensively studied, and the risks with an MR exam are low, particularly if the subject qualify for the testing based upon the screening questions. Participants, however, may be bothered by feelings of confinement (claustrophobia), and by the noise made by the magnet during the procedure. To minimize discomfort, participants will be asked to wear earplugs or earphones while in the magnet. Participants cannot receive an MRI if they have a pacemaker, an implanted defibrillator or certain other implanted electronic or metallic devices. Every participant who qualify for MRI testing will be asked to report any history of brain surgery for a cerebral aneurysm, implanted medical or metallic devices, shrapnel, or other metal, such as metal in the eye. If the MRI compatibility of any metal implant cannot be established, it will be considered a contraindication.

Risk of Genetic Testing.

The risk of genetic testing is quite low because only genes that are related directly or indirectly with UA metabolism will be characterized in this protocol. Although there can be no absolute guarantees, every reasonable effort will be made to keep personally identifiable information secret so there will be no misuse. During the consenting process, we advise participants that if they are asked if ever been tested for a genetic disorder, they should respond “no” since the results of these tests are done for pure research purpose and are not systematically complemented by the collection of other medical information that make them clinically relevant. The privacy of the research information generated from this study are protected and considered highly confidential.

Risk/Benefit Assessment: There is a high societal Benefit/Risk Ratio in this study. We may be able to ascertain if UA increases pro-inflammatory biological substances or contrarily leads to a protective increase of antioxidant substances.

Risk Associated with Stored Specimens: The greatest risk associated with stored specimens is the unplanned release of information from the subject’s medical records. The chance that this information will be given to an unauthorized person without the subject’s permission is very small. Possible problems with the unplanned release of information include discrimination when applying for insurance or employment. Similar problems may occur if the subject discloses information himself or agrees to have his medical records released.

Risk Associated with HIV Testing:

This study requires that your blood be tested for blood-transmitted diseases such as hepatitis virus B, hepatitis virus C, and human immunodeficiency virus (HIV) during the screening visit. You will be informed of the results of these blood tests regardless of your participation in this study.

Human immunodeficiency virus (HIV) test: A separate consent for HIV testing will be explained to you and HIV test will be done during the screening visit (visit #1) only.

If your HIV test is positive:

- A copy of the Department of Health and Mental Hygiene’s publication “Information for HIV Infected Persons” will be provided;
- The local health department or your doctor will offer advice about services which are available;
- Information will be provided on how to keep from transmitting HIV infection;
- Your Unique Identifying Number (UI) will be given to the health department;
- Your name will be reported to the local health department when your doctor finds that you have symptoms of HIV disease or AIDS;
- The local health department or your doctor will offer assistance in notifying and referring your partners for services. If you refuse to notify your partners, your doctor may notify them or have the local health department do so. If local health department staff notifies your partners, your name will not be used. Maryland law requires that when the local health department knows of your partners, it must refer them for care, support, and treatment.

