**Visit 1: Screening Tests**

Prior to attending the screening visit, each potential participant will be asked to fast overnight (> 8 hours). This screening visit will be conducted under the NIA Uric Acid protocol number 2008-322. After the reviewing the study schema in detail and obtaining protocol, HIPAA, and HIV consents, potential participants will be screened for study eligibility by assessing medical history, physical examination, blood draw (26.5 ml), routine urinalysis, vital signs, height and weight (used to compute BMI) and waist circumference. EKG will be performed at baseline. Cognitive status will be assessed using the Blessed Mental Test and potential participant with a score> 3 will be excluded. Complete CBC with differential count, glucose, BUN, creatinine, UA, LDH, CPK, electrolytes (Na+, K+, Cl-; Ca++, Mg+), AST, ALT, ALP, albumin, globulin, bilirubin (total and direct), haptoglobin, HDL-LDL and Total cholesterol, triglycerides, and CRP will be estimated from blood samples. We will also test for HCV, HBV and HIV. The Glucose-6-Phosphate Dehydrogenase activity will be assessed in each eligible participant randomly assigned to Trial B (individuals who are glucose-6-phosphate dehydrogenase deficient cannot break down hydrogen peroxide, a byproduct of rasburicase, leading to hemolysis). In addition, we will tests potential participants for drug use (urine toxicology test). Urine analysis will be also performed to rule out urinary infections. Finally, urine pregnancy tests will be performed on all women of childbearing age. Since the average age of menopause in the U.S. in 51±4.1 years, all women under age 60 will be considered of childbearing age, with the exception of those who have had their uterus surgically removed. All these tests are aimed at screening for conditions that are considered exclusion criteria for this study, and are performed according to standard clinical methods. A physician will review subject’s medical history, physical exams, EKG and biological tests in order to evaluate the participant’s eligibility criteria. Subjects who are found to be eligible for the study will be scheduled for Visit 2. Those assessed as ineligible will be notified within one week. When notified of eligibility, participants will be instructed on NPO criteria for Visit 2. The participants will receive the following instructions written on an hand-out: 1. To maintain the same dietary habits they had before being involved in the study; 2. In particular not to change their dietary habits by increasing high-purine sea foods, such as anchovies, sardines, herring, mackerel, and scallops, high-purine meats, such as game meats, liver, beef, kidney, brains, meat extracts (e.g. Oxo, Bovril), meat gravys, pork, poultry, and sweetbreads, and high-purine vegetables, such as asparagus, green peas, cauliflower, spinach and mushrooms, lentil, dried peas and beans, and to continue to consume vegetables, oatmeal, wheat bran and wheat germ in the same portions as before. Participants will be advised that changes in their habitual diet may result in a substantial change of their circulating UA levels and that, if so, their participation in the study will be discontinued.

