
**Visit 2: history, physical exam and preliminary test**

Participants will arrive at NIA Clinical Research Unit after overnight fasting for 8 hours. A brief physical examination will be performed, including a sample of blood that will be collected for DNA extraction and characterization of the genes that indirectly or directly affect the UA metabolism. A physician will review subject’s eligibility criteria and immediately after the participant will be administered an MRI-spectroscopy that estimates the rate of phosphocreatinine resynthesis after exercise). Next, an Oral Lipid Tolerance Test (OLTT) will be performed. The OLTT consists of eating a standard fast-food type meal (with approximately 900 cal and 50 grams of fat), and measuring changes in lipids and inflammatory markers at 2 hour intervals for total of 8 hours. The meal will be prepared by a registered dietitian and will be consumed in no longer than 20 minutes. The inflammatory markers that will be sampled consist of IL-6, IL-6sr, TNF-α, TNF-r1, TNF-r2, sgp 130, and hsCRP (+Tryglycerides). However, based on the information available at the end of the study, some of these inflammatory markers may not be measured and may be substituted with markers without changing the quantity of blood collected. OLTT will start in the morning after 8 hours of fasting. After the meal, subjects will not eat for the next 8 hours but will have free access to water and ice. After 8 hours a standard meal will be available. Blood samples will be drawn before the meal and every 2 hours after the first bite of the meal over an 8-hour period. The total amount of blood needed for the tests/assays included in the OLTT will be 40 mL including a 1mL waste at each time point. The blood will be sent via courier to NIA Lab at the 2 hour intervals. From there the blood will be sent to the respective labs for processing. After discharge, the patient will be given instruction for the following visit. In particular, participants will be advised to drink 8 8oz glasses of water on the day before the visit and at least 2 further glasses in the morning before the infusion.

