**13. COLLECTION AND STORING OF HUMAN SAMPLE SPECIMENS**

Intended Use of the Sample/Data: Samples and data collected under this protocol may be used to study baseline health of the participant and laboratory values will be used to investigate inflammatory and antioxidant markers before, during and after treatment as above specified. Genetic testing will be preformed. Any other research or experimental treatments will be done under other protocols for which separate IRB review and approval will be obtained.

Labeling of Stored Samples: The subject’s stored samples will be labeled at the time of collection with the participants study code, visit number and visit date so that only the study team can link them to the subject. Any identifying information about the subject will be kept confidential to the extent required by law.

How Samples/Data will be tracked: Samples/data will be tracked using the NIA Biological Sample Inventory system following NIH guidelines. Any other research that may use the banked samples other than the research described in this protocol will be done under other protocols for which a separate IRB review and approval will be obtained.

Storage and Release of Samples: Samples of the subject’s blood will be kept in a research laboratory at the National Institutes of Aging, NIH, or one of our contract facilities. The subject’s samples may be tested immediately, or they may be frozen and analyzed later. Samples may be kept until no residual specimens remain, or until the investigators decide to destroy them. If the subject gives us permission, some samples may be released to other doctors and scientists who are not associated with this institute. The Clinical Director and the Principal Investigator on this protocol will decide which researchers may receive samples. The subject’s samples may be used in their research only if the research has been approved by an Institutional Review Board (IRB) and is related to the original research questions associated with this protocol.

We will code the blood and urine samples so that we will keep the subject’s identity confidential. We will retain a code list that enables us to link the clinical information and results on each sample to the subject. The biological assays performed on these samples are described in the protocol.

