**17. BENEFITS**

This is not a treatment study, and the subjects are not expected to receive any direct medical benefits from their participation in the study. However, there is an expectation that the information from this study may lead to a better understanding about the relationship between UA and chronic inflammation. The comprehensive testing done through the study will provide valuable information to the subjects involved. Only results of tests that are medically relevant, mostly those collected in the eligibility phase of the study, will be communicated to the participants.

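### The consent advice to deny ever having been tested for a genetic disorder is misleading as written and makes no exception for the clinical G6PD test

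*Protocol*

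**What the plan says.** Section 6, under the risk of genetic testing, describes what participants are told while consent is taken: "we advise participants that if they are asked if ever been tested for a genetic disorder, they should respond" that they have not. The reason follows directly: "since the results of these tests are done for pure research purpose and are not systematically complemented by the collection of other medical information" that would make them clinically relevant. The paragraph opens by stating that "only genes that are related directly or indirectly with UA metabolism will be characterized in this protocol".

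Two other places describe the genetic work. At Visit 2 a blood sample is "collected for DNA extraction and characterization of the genes that indirectly or directly affect the UA metabolism". Section 13 says plainly: "Genetic testing will be preformed".

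The protocol also contains a test for G6PD deficiency. Section 4b lists the deficiency as exclusion criterion 9, and a footnote to the criteria describes a test for it needing 3.5 ml of blood. Section 5, Visit 1, says "The Glucose-6-Phosphate Dehydrogenase activity will be assessed in each eligible participant randomly assigned to Trial B" and gives the reason: "individuals who are glucose-6-phosphate dehydrogenase deficient cannot break down hydrogen peroxide, a byproduct of rasburicase, leading to hemolysis". On results, Section 17 says "Only results of tests that are medically relevant, mostly those collected in the eligibility phase of the study, will be communicated to the participants".

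**The concern.** The advice supplies a fixed answer to a broad question. It does not say who might be asking, and it does not separate research genotyping from tests done for eligibility. The protocol performs both kinds of test. A participant who remembers the advice will remember the question and the answer, not the paragraph heading under which it was written.

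Two things are at stake. The first is the accuracy of what participants are told at consent: the stated reason supports explaining that the DNA work is research, but it does not support denying that testing took place. The second is narrower. A person found to be G6PD deficient has a result that the protocol itself links to haemolysis, and nothing in Section 6 says that the advice stops short of that result.

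**Working it through.** No arithmetic applies beyond counting, so the check is a comparison of the passages.

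1. **What the advice rests on.** Section 6 does not claim that no test was done. It claims that the tests are research and not clinically relevant. The advice is therefore sound only if that description fits every test to which a participant could reasonably apply it.

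2. **The DNA work.** Visit 2 collects DNA to characterise genes bearing on uric acid metabolism, and Section 13 calls this genetic testing. The research description fits. No genetic disorder is named, so a denial of having been tested for a genetic disorder is not demonstrably false. It is misleading, because the participant has had genetic testing and is told to give an answer that most listeners would take to mean otherwise.

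3. **The G6PD test.** Compare it with each part of the stated reason.
 - *Purely research?* No. It tests for exclusion criterion 9. The Visit 1 text describes the screening tests, G6PD among them, as aimed at exclusion conditions and done by standard clinical methods.
 - *Not clinically relevant?* No. The Visit 1 text justifies it by haemolysis with rasburicase.
 - *Results not returned?* Section 17 returns medically relevant results, mostly from the eligibility phase. It does not name G6PD, so return of this result is a plausible reading and not an explicit statement.

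 The stated reason therefore fails for this test, and Section 6 contains no exception for it.

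4. **Who is affected.**
 - The advice is given at consent, which takes place at screening. Those who hear it can exceed the 40 planned completers (2 trials × 20), and Section 9 sets an accrual ceiling of 200.
 - The misleading element concerns those who reach Visit 2 and have DNA characterised.
 - The G6PD element concerns those assigned to Trial B: 20 planned, plus anyone tested and then excluded or replaced.
 - A safety consequence could arise only among those found deficient. The protocol gives no prevalence, so no number is offered.

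**The case against.** The strongest reply is about scope. The advice sits under the heading on genetic testing, the paragraph limits itself at once to uric acid metabolism genes, and the tests it refers to are most naturally the Visit 2 DNA work. G6PD is measured as enzyme activity during eligibility screening, and the protocol never calls it a genetic test or the deficiency a genetic disorder. On that reading the research reason was never written about G6PD, and what is left is a missing exception. Most of this stands. It is why the G6PD part is put here as a consequence of unqualified wording and not as a direct contradiction. It does not remove the point, because the scripted question is broader than the paragraph and a participant told of a G6PD deficiency could reasonably apply the advice to it.

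A reader might infer several stronger things that the protocol does not support:
- *That the answer is untrue for everyone genotyped.* No disorder is named, so misleading is as far as the text goes.
- *That the advice is unsafe for everyone tested for G6PD deficiency.* A person with a normal result conceals no risk, and those found deficient are excluded from the trial.
- *That participants are coached to mislead clinicians.* Section 6 does not say who is asking. The sentences around the advice concern confidentiality and misuse of information, and the later paragraph on stored specimens mentions insurance and employment.
- *That the advice cancels the value of a returned result.* It concerns having been tested. It tells nobody to deny a known diagnosis.

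Finally, the consent form is not among the documents at hand, so whether it already limits the advice or treats G6PD separately cannot be checked.

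**Conclusion.** The advice is wrong as written, and the severity is minor. It gives participants an unqualified denial that is misleading for those whose DNA is characterised. Read literally, it is wrong for Trial B participants tested for G6PD deficiency, because the reason offered does not fit a clinical exclusion test done for haemolysis risk.

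The G6PD part rests on two assumptions: that a participant takes the unqualified wording at face value, and that G6PD deficiency counts as a genetic disorder, which is general knowledge and not stated in the protocol. Any safety consequence is limited to people found deficient, and their number cannot be derived from the protocol. Nothing here affects allocation, endpoints, analysis or power.

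**What to change.** In Section 6, delete the advice on how to answer the question, and delete any matching sentence in the consent form. Put two statements in its place:
- The DNA characterisation of genes related to uric acid metabolism is done for research and is not a clinical diagnosis.
- That statement does not cover the G6PD test, which is a clinical eligibility test whose result is handled under Section 17.

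Do not add an assurance that DNA results stay out of the medical record, because the protocol does not say so.

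The cost is about two sentences in Section 6 and the corresponding consent text. Procedures, blood volumes, sample size and analysis are unchanged.
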